### Randomization and allocation concealment

Participants will be randomly assigned in a 1:1 ratio to the intervention group or the control group. The random allocation sequence will be generated by an independent statistician using computer-generated block randomization. Group assignments will be placed in sequentially numbered, opaque, sealed envelopes prepared by personnel not involved in recruitment, treatment or outcome assessment. After baseline assessment and confirmation of eligibility, the next envelope in sequence will be opened to reveal treatment allocation.

### Implementation

Potential participants will be screened and enrolled by study investigators at the trial site who are responsible for recruitment and baseline assessment. These investigators will not have access to the random allocation sequence in advance. The random sequence will be generated by an independent statistician and implemented through sequentially numbered, opaque, sealed envelopes. After eligibility confirmation and completion of baseline assessment, the next envelope in sequence will be opened by designated study personnel to assign the participant to the allocated intervention. Treating therapists and outcome assessors will not have prior access to the allocation sequence.

### Blinding

Because the two interventions differ clearly in content and delivery, blinding of participants and treating therapists is not feasible. To minimize bias, outcome assessors, ultrasound examiners, and statisticians will remain unaware of treatment allocation, and participants and their guardians will be reminded not to disclose group assignment during outcome assessments.

Unblinding of blinded study personnel will be permitted only when knowledge of treatment allocation is necessary for participant safety or urgent clinical management. Any unblinding will be decided by the principal investigator, documented with the reason, and restricted to the minimum personnel necessary. Data analysts will remain blinded until the main analysis is completed whenever possible.

### Interventions

All interventions will be delivered by licensed therapists with formal clinical training in pediatric cervical rehabilitation and manual therapy. Before treating trial participants, all treating therapists will receive protocol-specific training on participant positioning, intervention procedures, progression rules, safety precautions, and documentation requirements. Only therapists who have completed the study training and demonstrated familiarity with the treatment manual will be permitted to deliver the study interventions. The study team will use a standardized treatment manual to improve consistency across sessions.

#### Control group: Joint mobilization.

Participants in the control group will receive joint mobilization therapy targeting the atlantoaxial joint and adjacent upper cervical segments. The procedure will include gentle traction mobilization, static segmental mobilization, and dynamic upper cervical mobilization.

During traction mobilization, participants will be placed in the supine position. The therapist will support the occipital region and mandible and will apply gentle cervical traction combined with controlled flexion, extension, lateral flexion, and rotation. Each movement will be repeated five times, with each stretch lasting approximately 6 s.

During static mobilization, participants will be placed in the sitting position. The therapist will apply rhythmic posterior-to-anterior pressure to the cervical spinous processes and bilateral transverse processes, together with vertical and lateral mobilization of the cervical segments. Each maneuver will be repeated five times, with each stretch lasting approximately 6 s.

During dynamic mobilization, participants will remain seated with the neck slightly flexed. The therapist will stabilize the occiput and apply gentle anterior gliding mobilization to C2, followed by small-amplitude rhythmic mobilization of the upper cervical segments. The end position will be maintained for at least 10 s when tolerated. Mobilization intensity will be adjusted according to each participant’s symptoms and tolerance.

Each session will last approximately 10–15 min. Treatment will be performed three times per week for 4 consecutive weeks, for a total of 12 sessions.

#### Intervention group: Joint mobilization plus cervical resistance training.

Participants in the intervention group will receive the same joint mobilization procedure as the control group, followed by structured cervical resistance training designed to improve muscle activation, neuromuscular control, and dynamic cervical stability.

Before resistance training, selective activation of the deep cervical flexor muscles will be performed in a supine crook-lying position with gentle cranio-cervical flexion while neutral cervical alignment is maintained. Light tactile cueing may be used to reduce substitution by superficial cervical muscles. This preparatory part will usually include 2–3 sets of 5 repetitions.

Manual resistance exercise will then be performed in four directions: flexion, extension, rotation, and lateral flexion [15,16,18]. All exercises will be isometric, with the cervical spine kept in a neutral position. Each contraction will be held for 5–8 s, followed by 5–10 s of rest. Participants will complete 8–10 repetitions per set and 2–3 sets in each direction. Resistance will be applied manually by the therapist. It will be progressed according to tolerance, symptom response, and movement control by adjusting therapist-applied resistance, contraction duration, or repetition number. Maximal effort testing will not be used. Training will be stopped or modified if pain rises clearly, compensatory movement becomes obvious, or the child cannot maintain the required position. Each treatment session will last about 15–20 min.

#### Frequency and duration.

Both groups will receive treatment 3 times per week for 4 consecutive weeks, for a total of 12 sessions.

#### Concomitant care and prohibited treatments.

During the intervention period, all participants will receive standardized education on posture, neck protection, and activity modification. Guardians will be advised to supervise daily behavior and to avoid excessive cervical rotation, sudden neck movements, prolonged head tilt, and other activities that may increase cervical stress or worsen symptoms. Routine daily care will be allowed as long as it does not interfere with the assigned intervention. No additional cervical immobilization will be prescribed as part of the study intervention. In the intervention group, no extra home-based neck strengthening exercises outside the study program will be allowed.

To reduce confounding, both groups will not receive other non-study cervical treatments during the intervention period. These treatments include manual therapy, traction, acupuncture, massage, structured rehabilitation outside the protocol, and invasive cervical procedures. Usual medication that is judged necessary for safety may still be used and will be recorded.

#### Adherence monitoring.

Treatment attendance will be recorded for all supervised sessions. Guardians in both groups will complete brief logs documenting cooperation with study instructions and any non-study cervical treatments. Adherence will be reviewed weekly by study staff. Important deviations from the assigned intervention, including missed treatment sessions or receipt of prohibited co-interventions, will be recorded. If major non-adherence occurs, adherence data will be summarized descriptively and considered in sensitivity analyses.

#### Protocol clarification.

The original ethics-approved clinical trial protocol in Chinese is provided as S1 File, and its complete English translation is provided as S2 File. It specified a single-center randomized controlled design, 70 participants, joint mobilization as the control intervention, joint mobilization combined with cervical resistance training as the intervention, a 4-week treatment period with 3 sessions per week, and follow-up at 3 and 6 months after treatment. In this manuscript, several reporting clarifications were made to meet clinical trial reporting standards. Affected-side sternocleidomastoid stiffness at week 4 was specified as the primary ultrasound-based endpoint based on the SWE-based cervical muscle elasticity outcome listed in the original protocol. The ultrasound analysis in this manuscript focuses on the sternocleidomastoid and upper trapezius muscles because these muscles are more directly related to torticollis presentation and can be measured more reproducibly in children. FPS-R and Pediatric NDI were used as pediatric-adapted measures of pain and neck disability, and week 2 was added as a non-primary interim assessment point to describe short-term changes during treatment. This additional assessment will not be used for the primary efficacy conclusion. These clarifications did not change the intervention framework, sample size, or overall study objective.

### Outcome measures

Outcome assessments will be conducted at baseline, week 2, week 4, and at 3 and 6 months after treatment. Week 2 will be used as an interim assessment point, while week 4 will be the end-of-treatment assessment point. The 3- and 6-month follow-up visits will be used to assess longer-term clinical outcomes and recurrence-related outcomes.

The primary outcome is affected-side sternocleidomastoid muscle stiffness at week 4 measured by shear-wave elastography and expressed as Young’s modulus (kPa). The primary comparison will be the between-group difference at week 4 after adjustment for baseline stiffness. The affected side will be defined before randomization according to the clinically dominant side of torticollis and muscle tightness, supported by baseline physical examination and imaging findings.

#### Ultrasound assessment procedures.

Ultrasound examinations will be performed using a Supersonic Aixplorer system (Supersonic Imagine, France) equipped with a 4–15 MHz linear-array transducer in musculoskeletal mode. For sternocleidomastoid assessment, participants will lie supine with the cervical spine in a neutral position and the neck muscles relaxed. For upper trapezius assessment, participants will be positioned prone without a pillow, with the hands placed beneath the forehead to promote relaxation of the posterior cervical region. Sternocleidomastoid measurements will be obtained at the midpoint between the sternal head and the mastoid process, and upper trapezius measurements will be obtained 2 cm lateral to the C4 spinous process. After acquisition of a stable grayscale image, the system will be switched to shear-wave elastography mode. A region of interest covering the target muscle will be selected, and Young’s modulus (kPa) will be recorded. Three measurements will be obtained on each side and averaged for analysis. All examinations will be performed by a trained assessor using a predefined standardized scanning protocol [29,30].

#### Secondary outcomes.

(1) bilateral sternocleidomastoid and upper trapezius SWE parameters;(2) pain intensity measured by the Faces Pain Scale-Revised (FPS-R);(3) cervical disability measured by the Pediatric Neck Disability Index (Pediatric NDI);(4) cervical rotation range of motion;(5) recurrence-related outcomes at 3 and 6 months after treatment;(6) overall clinical efficacy at week 4.

#### Shear-wave elastography parameters.

SWE will assess the bilateral sternocleidomastoid and upper trapezius muscles at baseline, week 2, and week 4. These data will describe broader changes in cervical muscle mechanics during recovery and will support the interpretation of the primary outcome [30,31].

#### Faces pain scale-revised.

Pain intensity will be measured with the Faces Pain Scale-Revised, which is a validated self-report scale widely used in children. Scores range from 0 to 10, and higher scores indicate more severe pain. Pain will be assessed at baseline, week 2, week 4, and at 3 and 6 months after treatment.

#### Pediatric neck disability index.

Cervical disability will be measured with the Pediatric Neck Disability Index. The same language version and scoring method will be used at all assessment time points. A guardian may help the child understand the questions when needed, but the child will provide the response whenever possible. This outcome will be assessed at baseline, week 2, week 4, and at 3 and 6 months after treatment.

#### Cervical rotation range of motion.

Active cervical rotation range of motion on both sides will be measured using a standardized clinical goniometric method while the participant sits in a consistent position. Two measurements will be obtained on each side, and the average value will be used for analysis. This outcome will be assessed at baseline, week 2, and week 4.

#### Clinical efficacy evaluation.

Overall clinical efficacy will be evaluated at week 4 according to standardized criteria derived from the Diagnostic and Therapeutic Criteria for Traditional Chinese Orthopedic Diseases and the Criteria for Diagnosis and Evaluation of Clinical Disease Outcomes. Treatment response will be classified into three categories: (1) Recovered: complete resolution of pain, normal cervical appearance, normal cervical range of motion, and no impact on daily life; (2) Improved: marked reduction in pain, no obvious cervical tilt, mild limitation of cervical motion, and minimal impact on daily life; (3) Ineffective: slight reduction in pain, persistent obvious cervical tilt, significant limitation of cervical motion, and noticeable impact on daily life.

The overall treatment effectiveness rate will be calculated as follows:

$$\begin{array}{c} Effectiveness\text{\textasciitilde{}}rate\left(\%\right)=(number\text{\textasciitilde{}}of\text{\textasciitilde{}}recovered\text{\textasciitilde{}}cases+number\text{\textasciitilde{}}of\text{\textasciitilde{}}improved\text{\textasciitilde{}}cases)/total\text{\textasciitilde{}}number\text{\textasciitilde{}}of\text{\textasciitilde{}}participants\times 100\%\text{.} \end{array}$$

#### Recurrence-related outcomes.

Recurrence-related outcomes will be assessed at 3 and 6 months after treatment. Recurrence will be defined as the return of painful torticollis and limited cervical rotation that leads to additional medical evaluation or treatment during follow-up. Investigators will collect this information during follow-up contact and review of available medical records.

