**Methods:**

This is a single-center, assessor- and analyst-blinded, randomized controlled superiority trial with two parallel groups. Seventy children aged 2–18 years with clinically and radiologically confirmed AARS will be randomly assigned in a 1:1 ratio to joint mobilization plus cervical resistance training or joint mobilization alone. Both groups will receive treatment 3 times per week for 4 weeks. The primary outcome is affected-side sternocleidomastoid stiffness at week 4 measured by SWE and adjusted for baseline stiffness. Secondary outcomes include bilateral sternocleidomastoid and upper trapezius SWE parameters, pain intensity, cervical disability, cervical rotation range of motion, overall clinical efficacy, and recurrence-related outcomes. SWE outcomes will be assessed at baseline, week 2, and week 4. Pain and disability outcomes will be assessed at baseline, week 2, week 4, and at 3 and 6 months after treatment. Cervical rotation range of motion will be assessed at baseline, week 2, and week 4. Recurrence-related outcomes will be recorded at the 3- and 6-month follow-up visits.

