## Methods

### Study design

This study is a single-center, randomized, controlled, two-arm, parallel-group superiority trial. Outcome assessors, ultrasound evaluators, and statisticians will remain blinded to group allocation. Because the two interventions differ clearly in content and delivery, participants and treating therapists cannot be blinded. Fig 1 shows the schedule of enrollment, interventions, and assessments, and Fig 2 shows the study flow.

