### Trial oversight

This is a single-center investigator-initiated trial coordinated by the Department of Tuina, Hangzhou Hospital of Traditional Chinese Medicine. The study team will be responsible for participant screening, recruitment, intervention delivery, outcome assessment, data collection and study coordination. The principal investigator will have overall responsibility for trial conduct and protocol compliance. No separate steering committee or endpoint adjudication committee has been established because this is a single-center trial with a modest sample size and low-risk physical interventions. Data management and quality control will be conducted by the study investigators according to predefined study procedures.

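### The protocol does not show that its assessor blinding covers recurrence, which investigators ascertain partly from medical records with no masking described

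*Protocol article*

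**What the plan says.** The abstract describes a "single-center, assessor- and analyst-blinded, randomized controlled superiority trial". Under Study design, "Outcome assessors, ultrasound evaluators, and statisticians will remain blinded to group allocation". The Blinding section repeats that "outcome assessors, ultrasound examiners, and statisticians will remain unaware of treatment allocation" and adds that "participants and their guardians will be reminded not to disclose group assignment during outcome assessments". Neither section excepts any outcome. The Blinding section also accepts that "blinding of participants and treating therapists is not feasible".

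Recurrence is listed among the secondary outcomes, and the Statistical analysis section compares it between arms at 3 and 6 months by chi-square or Fisher's exact test. Its definition reads: "Recurrence will be defined as the return of painful torticollis and limited cervical rotation that leads to additional medical evaluation or treatment during follow-up". On ascertainment the protocol says: "Investigators will collect this information during follow-up contact and review of available medical records".

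Two further sections bear on this. Trial oversight gives treatment delivery, outcome assessment and data collection to the study team as a whole and states: "No separate steering committee or endpoint adjudication committee has been established". Trial monitoring has the study investigators monitor the trial, with adherence records among the items reviewed at least monthly during active recruitment and treatment.

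**The concern.** The blinding statement is a list of roles, and the role named for recurrence is not on it. One of the two sources for recurrence is a record that could disclose the arm, and the only safeguard stated for assessments is asking families to stay silent, which does nothing about records.

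The outcome also needs judgement. Someone has to decide whether painful torticollis and restricted rotation came back, and whether that led to further care. Rotation is scheduled for measurement only up to week 4, so no planned measurement anchors the decision at 3 or 6 months. If the person asking and classifying knows the arm, how hard they probe and how they label borderline cases can differ between arms.

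At stake is the credibility of one of three efficacy outcomes that extend beyond week 4 (with pain and disability). The abstract's blinding label and the Discussion's listing of blinded outcome assessment as a strength also currently apply to recurrence without qualification.

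**Working it through.** The protocol states no recurrence rate and no figure that tests this point, so the main check sets sections against each other.

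**Step 1: who is blinded, and who collects recurrence.** Study design and Blinding name three blinded roles. The Recurrence-related outcomes section names investigators. The Implementation section uses investigators for those who recruit and do the baseline assessment, and mentions treating therapists and outcome assessors separately. The Data collection section, however, also has trained investigators recording study data in general. The word is therefore used loosely. It neither places the recurrence collectors outside the blind nor shows that they are inside it.

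**Step 2: is there a route to the allocation?** Two routes follow from the text.
- Study investigators monitor the trial, and adherence records are among the items reviewed.
- Medical records are read with no masking described. Each child has 12 sessions at one hospital department, so entries that reveal the arm are plausible. No section says what the records contain.

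**Step 3: is there a second line of defence?** There is no adjudication committee, and the reminder about disclosure addresses families only.

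**Step 4: what would blinding the classifier leave untouched?** The definition counts a return of symptoms only if it leads to evaluation or treatment. Families know the arm, and whether they seek care can depend on it. Blinded classification does not remove that.

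**Step 5: illustration of size.** Everything here except 35 per arm (Sample size section) is assumed. Let p be the true recurrence in both arms and c the fraction of events captured in one arm, with full capture in the other. Then

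false difference = p × (1 − c); expected children = 35 × p × (1 − c).

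| p | c | False difference | Children at 35 per arm | Two-sided Fisher rejection, no true effect |
|---|---|---|---|---|
| 10% | 100% | 0 | 0 | 1.3% |
| 10% | 80% | 2 points | 0.7 | 1.4% |
| 10% | 60% | 4 points | 1.4 | 2.3% |
| 20% | 100% | 0 | 0 | 2.5% |
| 20% | 80% | 4 points | 1.4 | 3.8% |
| 20% | 60% | 8 points | 2.8 | 8.5% |
| 30% | 100% | 0 | 0 | 2.8% |
| 30% | 80% | 6 points | 2.1 | 5.1% |
| 30% | 60% | 12 points | 4.2 | 14.5% |

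The rejection rates sum the binomial probabilities of all pairs of event counts for which Fisher's test gives P < 0.05. Incomplete capture in both arms can be treated the same way. With p = 20% and capture of 95% and 70%, the observed rates are 0.20 × 0.95 = 19% and 0.20 × 0.70 = 14%, a ratio of 0.74. That is 6.65 against 4.9 expected children, fewer than two events apart, with a rejection rate of 4.6%. The direction of any such bias is unknown.

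**The case against.** The strongest reply is that this is an unspecified role and not a contradiction. Outcome assessors are blinded with no exception, recurrence is a listed outcome, and investigators is this article's general word for trial staff, so the natural reading is that whoever assesses recurrence is blinded. Details of follow-up contact and record extraction may also be in the full ethics-approved protocol, supplied as supplementary files and not seen here.

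Much of this stands, and it rules out several stronger statements that a reader might infer:
- That recurrence is assessed unblinded. No section says so, and the collectors could be the blinded assessors.
- That the records contain the trial-treatment notes. This is plausible at a single treating site but nowhere stated.
- That recurrence is the only outcome entrusted to investigators. Implementation and Data collection give them other data, including the baseline assessment.
- That those who collect recurrence also deliver treatment. Trial oversight lists functions of the whole team, while the Interventions section assigns delivery to trained therapists.
- That a bias of a given size has been shown. The capture rates are assumptions, and only the more severe ones take the Fisher rejection rate well above 5%.

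The reply does not remove the core. The article goes beyond leaving a detail out: it states a method, in which investigators contact families and read records. That method, followed as written, can expose the arm to the person who classifies the outcome. The one stated safeguard at assessments does not reach the records.

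**Conclusion.** The point holds in a limited form. The blinding statements and the recurrence method are not reconciled, so the protocol does not show that its blinding covers recurrence. Record review could plausibly disclose the arm, on the assumption that the records at the treating site contain something about the sessions given.

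The consequence is confined to this outcome. The primary endpoint is measured by explicitly blinded ultrasound examiners, the sample size does not change, and the protocol treats secondary outcomes as supportive and exploratory. It is still worth correcting, because recurrence is compared between arms and the blinding claim is made for the trial without exception. Dependence on care-seeking by unblinded families is a separate limitation. It follows directly from the definition and remains whoever classifies the events.

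**What to change.** Replace the last sentence of the Recurrence-related outcomes section with wording such as: *A blinded outcome assessor will obtain recurrence information at each follow-up contact using a fixed script. Study staff who do not assess outcomes will extract the relevant medical-record entries on a standard form, with trial-treatment information masked. The blinded assessor will classify recurrence from the script and the masked extract.*

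If this cannot be done, state that recurrence is not assessed blind, and except it from the blinding label in the abstract and from the blinded-assessment strength in the Discussion.

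In either case, add to the limitations that recurrence as defined depends on families who know the allocation seeking further care, and that blinded classification does not remove this.

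The cost is a few sentences, a short extraction form and some clerical masking time for at most 70 children, using staff the trial already has. The unmasked extractor still chooses which entries to pass on; a standard form limits that but does not abolish it. Data collection is expected to run until 31/05/2027, so follow-up contacts made after the change would benefit. The sample size and the primary analysis are unaffected.
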